#### 4.7. ANALYSIS OF THE SECONDARY OUTCOMES

The primary outcome analysis will be adapted to the secondary clinical outcomes by the choice of a suitable regression model. Effect sizes, 95% confidence intervals, and p-values will be presented (**Table 3** and **Table 4**, see Section 5).

#### 4.8. MECHANISTIC ANALYSIS

The POCTRM result is a key potential mechanism on the causal pathway between availability of the POCTRM, the clinician's belief that an antibiotic is necessary and the decision to prescribe an antibiotic. We will conduct a mechanistic analysis on the per protocol sample. An interaction term will capture any difference in the effect of the test result on prescribing between the two randomly allocated groups who do and do not have the test result available to inform the clinical decision. In the logistic regression model:

$$\text{Log odds(antibiotic prescribed)} = [\text{Group}] + [\text{Virus detected versus not detected}] + [\text{Interaction}]$$

"Virus detected versus not detected" will be as determined by the practice POCTRM machine in the intervention group (i.e. the result that will inform the general practitioner's decision making), and as detected by the central study POCTRM machine in the comparison group. Note that any finding including detection of an atypical bacteria will be coded as "virus not detected" as better reflecting the likely influence of this result on decision making.

The null hypothesis for the interaction term is that the 'virus detected/not detected' result has the same effect on prescribing in the POCTRM (have the virus detected/not detected result to inform their prescribing decision) and comparison groups (do not have the result to inform their prescribing decision). The interaction term in the analysis model separates the effect of the POCT result from study clinicians' underlying ability to appropriately diagnose the need for an antibiotic without the POCTRM result. Whilst the POCT result is revealed to study clinicians and intervention group participants post-randomisation, the proportions of viral and bacterial infections will have been balanced by the randomisation, such that an interaction test from the standard regression model will give evidence of the causal role of the POCTRM test result (**Table 2**, see Section 5).

Clinician and participant views, pre-randomisation, will be tabulated by allocated group for the full analysis set (**Supplementary Table 3a, 3b; Supplementary Table 4a**, see Section 5). Clinician views, post-randomisation, will be tabulated by allocated group for the per protocol set, and the null hypothesis of no difference in the population in views between the two groups will be tested using an ordered logistic regression model (**Supplementary Table 4b**, see Section 5). Participant views, post-randomisation, will be tabulated by allocated group for the full analysis set, and the null hypothesis of no difference in the population in views between the two groups will be tested using an ordered logistic regression model (**Supplementary Table 3c, 3d**, see Section 5).

The result of the POCTRM test for each participant in the intervention group will be presented, with the probability of a prescription of antibiotic or of a antiviral for each observed result (**Supplementary Table 5**, see Section 5).

The change in response to the question “I believe an antibiotic is needed to treat the patient’s illness” for clinicians in the per protocol set is tabulated for the three groups, POCTRM virus detected, POCTRM no virus detected, no POCTRM group (**Supplementary Table 6**, see Section 5).

The aim of the primary results paper is to present information on the nature and magnitude of the effect of the POCTRM on clinical outcomes, and upon potential mechanisms for that impact on outcomes. These results will guide the scope and approach to a causal analysis of potential mechanisms for any clinical benefit of POCTRM, to be reported in a separate paper.

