## 6.6 Randomisation (Day 1)

### Figure 1, Step 4

Participants will be individually randomised 1:1 to intervention (GP POCTRM test) or control (No GP POCTRM test) using an internet-based randomisation system developed and maintained by Sealed EnvelopeTM. Randomisation will be stratified by age (<16 years vs. ≥16 years) and chronic lung disease (present vs. absent). It will not be possible to blind the allocated randomisation group since the subsequent processes for each group differ.

The Study Champion or Clinician randomises participants and immediately informs (if necessary) the Study Clinician which group the participant has been allocated to.

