#### 10.1.2 Mechanistic Sample Size

Next, we illustrate the power of a study with 244 in each group for investigating the hypothesis that a virus detected/not detected result is on the causal pathway between the POCTRM, the clinician's belief that an antibiotic is necessary and prescribing behaviour. The power calculation is based on an interaction term (capturing any difference in the effect of the test result on prescribing between the randomly allocated groups) in the logistic regression model:

$$\text{Log odds}(\text{prescription}) = [\text{Group}] + [\text{Virus detected vs. not detected}] + [\text{Interaction}]$$

The null hypothesis for the interaction term is that the 'virus detected/not detected' result has the same effect on prescribing in the intervention and control groups. The statistical power to test this hypothesis was evaluated in a simulation study outlined in Table 10. While the test result will not be made available to inform the clinical decision in the control group, the simulations allow for GPs being better than chance at prescribing antibiotics in cases who will benefit (microbial testing in the control group will allow us to observe if this is the case). Similarly, the interaction term in the analysis model separates the effect of the POCTRM from GPs' ability to appropriately prescribe.

Two scenarios are considered for the POCT group (Table 10). In Scenario One (Figure 5, red line) antibiotic prescribing is affected both when a virus is detected (prescribing reduced) and when a virus is not detected (prescribing increased to P1=90%). Note that this scenario is based on the prescribing changes observed in our feasibility study, and gives the absolute difference in prescribing between groups used in our sample size calculation (60% versus 45%). In Scenario Two (Figure 5, blue line) antibiotic prescribing is only affected when a virus is detected and not when no virus is detected (P1=75% as for the control group). Hence, the scenarios differ in the assumed probability of prescription P1.

**Table 10: Assumed Population (true) Antibiotic Prescribing Rates in Two Scenarios Forming the Basis of Simulation Studies to Determine the Statistical Power to Identify the Test Result is on the Causal Pathway**

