| Overall probability antibiotic prescribed                                   | 39%                                                                     | 60%                                                              |

a Proportions informed by feasibility study

The population probability of a prescription in those for whom the POCT identified a virus (Table 10, P2) was varied within each scenario. Assuming a population probability of prescription for 50% of participants in the control group for whom a virus would be identified, the x-axis of Figure 5 presents prescribing as a relative risk P2/50%. Following the example in Table 10, P2 = 15%, the true effect of detecting a virus is a relative risk of 0.3 i.e. a 70% reduction in prescribing in this subgroup.

For each of the two scenarios, 1000 simulated datasets were generated for values of P2 from 0.20 to 1.00. For each simulation, the “observed” probability of detecting a virus, and each of the four prescription probabilities, were generated according to a binomial distribution. The above logistic regression model was fitted to each dataset, and the p-value for the interaction term calculated using a likelihood ratio test. The power (Figure 5, y-axis ) for each combination of scenario and P2 was calculated as the percentage of p<0.05.

Figure 5 shows that, for both scenarios, 244 participants per group provides >90% power to detect an effect of the test result of at least a 60% relative reduction in prescribing among the test positives. Hence the proposed trial is large enough to identify dichotomised mechanisms on the causal pathway, with greater power expected for mechanisms measured on a scale.

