## 10.2 Statistical Analysis

A detailed statistical analysis plan will be finalised and made publicly available ahead of the completion of recruitment. The primary analysis will be of observed data and conducted according to the intention to treat principle. A logistic regression equation will estimate the causal association between the primary outcome of antibiotic prescribing and allocated intervention group as an odds ratio, presented with 95% confidence interval and p-value. Further covariates will include participant age and chronic lung disease (used to stratify randomisation). Variations between participating GPs in prescribing tendency will be accommodated e.g. dummy variables to distinguish each GP. Sensitivity analyses will gauge the robustness of the conclusions to different assumptions about missing data. The above approach will be adapted e.g. through the choice of a suitable regression model, to the secondary outcome variables such as symptom severity at 2 to 4 days.

As described for the statistical power analysis, whether the result of the POCTRM influences prescribing of an antibiotic will be investigated in a logistic regression model with covariates including allocated group (results inform the clinical decision or not), result (virus detected or not), and the interaction between the two. The interaction term will capture any evidence that the test result is influencing the prescribing decision, rather than a non-specific effect of the POCTRM which is independent of the result, and distinguish this effect from any underlying ability of GPs to prescribe to those participants who will benefit from an antibiotic. Further investigations of the causal pathway will include the logistic regression model:

$$\text{Log odds}(\text{confident an antibiotic will benefit}) = \text{Group} + \text{Result} + \text{Interaction}$$

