### 4.4. SUBGROUP ANALYSES FOR PRIMARY OUTCOME

Three pre-specified subgroup analyses will be conducted for the primary outcome (**Table 2**, see section 5):

Age <16 years versus 16+ years. We hypothesize that, due to less information about symptoms being provided by children, the information from the POCTRM will reduce antibiotic prescriptions to a greater extent in children.

Presence or absence of chronic lung disease. We hypothesize that general practitioners will tend to “play it safe” and prescribe an antibiotic to those with chronic lung disease, and there will be less of an impact of the POCTRM on antibiotic prescribing in that group.

Disagreement (or not) between the general practitioner and the patient in whether an antibiotic is needed. We hypothesize there will be a greater impact of the POCTRM in reducing antibiotic prescribing when the patient believes an antibiotic is needed (agree or strongly agree with this statement) but the general practitioner strongly disagrees or disagrees that an antibiotic is needed,

or is uncertain. In this situation, evidence from the POCTRM that the RTI may have a viral cause may reduce the likelihood of the general practitioner being persuaded to prescribe an antibiotic.

If there is evidence of superiority for the POCTRM group compared to the control group on the key secondary outcome of symptom severity over days 2 to 4, the above subgroup analyses will also be conducted for that measure (and presented in a separate supplementary table).

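### Randomising allocation does not by itself let the Group × Virus interaction show that disclosure of the POCT result drives prescribing; the plan should state the extra assumption and add one sensitivity model

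*Combined protocol and SAP*

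**What the plan says.** SAP 4.8 fits a logistic model for antibiotic prescription in the per protocol set, with terms for allocated group, virus detected or not, and their interaction. Virus status comes from the practice machine in the intervention arm and from the central machine in the comparison arm. The SAP accepts that the result is revealed after randomisation. Its premise is that "the proportions of viral and bacterial infections will have been balanced by the randomisation". The conclusion it draws from this premise, about what the model can show, is worded "such that an interaction test from the standard regression model will give evidence of the causal role of the" test result. SAP Table 2 labels this row a causal mechanistic analysis. Its footnote a adjusts odds ratios for age and chronic lung disease, so these enter at most as main effects.

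Protocol 10.2 makes the same claim in stronger terms: "The interaction term will capture any evidence that the test result is influencing the prescribing decision, rather than a non-specific effect of the" POCT that does not depend on the result. It adds that the term is separated from clinicians' unaided ability to prescribe well.

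Only allocation is randomised. Protocol 6.6: "Randomisation will be stratified by age (<16 years vs. ≥16 years) and chronic lung disease (present vs. absent").

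Protocol 10.1.2 supplies the power: "244 participants per group provides >90% power to detect an effect of the test result of at least a 60% relative reduction in prescribing" among virus-positive patients.

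**The concern.** Two statements are being treated as one. The first is that the effect of POCT on prescribing differs between virus-positive and virus-negative patients. Randomising the group supports that, because within each virus stratum the arms are comparable. The second is that the effect differs because the clinician saw the result. Virus status is a patient characteristic, not something assigned. Patients with and without a virus may differ in age, lung disease or how convinced the clinician was beforehand. If having the test changes prescribing for reasons other than its result (the pause, the second contact, a feeling of reassurance), and does so more in one kind of patient, and that kind is more often virus-positive, the interaction is non-zero even when nobody acts on the result.

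The model removes two things: clinicians' unaided ability (through the main effect of virus) and a non-specific effect that is constant on the odds scale. It does not remove a non-specific effect that varies with something linked to virus status. At stake is the only formal test of the result mechanism planned for the primary paper.

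**Working it through.** **Inputs from the documents.** There are 244 per group ("Next, we illustrate the power of a study with 244 in each group", Protocol 10.1.2). Virus is detected in 60%. Control prescribing is 75% without and 50% with a virus, 60% overall, and the overall POCT rate in Scenario One is 45% (Table 10). The interaction is tested by likelihood ratio at 5%.

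**1. The plan's own power.** A 60% relative reduction makes prescribing in virus-positive POCT patients 0.4 × 50% = 20%. Simulation of the planned model (10,000 datasets) gives 99.98% power in Scenario One and 90.8% in Scenario Two, so the stated figure of over 90% is reproduced. The ratios of odds ratios (virus-positive over virus-negative) are:
- Scenario Two: (0.20/0.80)/(0.50/0.50) = 0.25, over 1, giving 0.25.
- Scenario One: 0.25 over (0.90/0.10)/(0.75/0.25) = 3, giving 0.083.

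**2. What the model does handle.** With no effect of the result and a constant non-specific odds ratio of 0.5, the test rejects in 5.0% of trials.

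**3. An effect unrelated to the result, in patients more often virus-positive.** The documents do not relate virus status to any baseline feature, so these values are assumed. Half of the cases have a clinician convinced at baseline that an antibiotic is needed. Virus is present in 40% of convinced and 80% of unconvinced cases. Control prescribing is 90% and 30% respectively. This reproduces Table 10:
- virus-positive: (0.2 × 0.90 + 0.4 × 0.30)/0.6 = 50%
- virus-negative: (0.3 × 0.90 + 0.1 × 0.30)/0.4 = 75%

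POCT then changes prescribing by baseline belief only, and the result is ignored. With 85% (convinced) and 5% (unconvinced) in the POCT arm:
- virus-positive: (0.2 × 0.85 + 0.4 × 0.05)/0.6 = 31.7%, odds ratio 0.463
- virus-negative: (0.3 × 0.85 + 0.1 × 0.05)/0.4 = 65.0%, odds ratio 0.619
- overall 45%; ratio of odds ratios 0.463/0.619 = 0.75

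The standard error of the log ratio is the square root of the sum of 1/[n p(1−p)] over four cells (n = 146.4 for virus-positive and 97.6 for virus-negative in each arm), which is 0.398. Then z = ln(0.749)/0.398 = −0.73, and the chance of p<0.05 is about 11%. Simulation gives 10-12%. The same steps for other settings, all with overall rates of 60% v 45%:

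| POCT-arm prescribing, convinced / unconvinced | Virus prevalence, convinced / unconvinced | Ratio of odds ratios | Planned test rejects |
|---|---|---|---|
| 85% / 5% | 40% / 80% | 0.75 | 11% |
| 88% / 2% | 40% / 80% | 0.67 | 17% |
| 80% / 10% | 40% / 80% | 0.90 | 6% |
| 75% / 15% | 40% / 80% | 1.08 | 5% |
| 85% / 5% | 50% / 70% | 0.86 | 7% |

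**4. Which adjustment helps.** In the first two rows, adding belief as a main effect only raises rejection, from about 10% to 18% and from about 17% to 33%. Adding Group × belief brings it to about 5%. A model with group interactions for belief, age and lung disease together also gives about 5%.

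**5. A second set of assumptions.** Take a feature present in half of patients, unrelated to control prescribing given virus status, with POCT acting only where it is present (odds ratio 0.28, about 60% v 46% overall). The planned test rejects in 7% of trials when virus prevalence is 70% v 50% with and without the feature, 19% at 80% v 40%, and 42% at 90% v 30%. Varying the odds ratio from 0.5 to 0.15 as well gives 6% to 65%, the top needing both extremes. Group × feature returns every setting to 5.1-5.5%.

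**6. Cost in power.** Under Scenario Two at 20%, adding the Group × feature term of step 5 lowers power from about 90% to 89%, 85% and 75% for the three prevalence contrasts. Scenario One stays at 99% or more. If belief is strongly prognostic, as in step 3, power for a 60% relative reduction rises instead, from about 91% to 98-99%.

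**The case against.** The strongest reply is that the documents do not predict the troublesome effect. A reader might take SAP 4.4 to show that the plan itself expects a non-specific effect varying by age. It does not. The subject of the age hypothesis is the information from the test, which "will reduce antibiotic prescriptions to a greater extent in children". The hypothesis on disagreement also runs through evidence of a viral cause, and the one on lung disease is about cautious prescribing. A reader might equally take Table 10 as proof of bias: "Assuming a population probability of prescription for 50% of participants in the control group for whom a virus would be identified", against 75% where none would be. That gap represents unaided clinical ability, and the main effect of virus absorbs it. Bias needs a further assumption that is not in the plan. Both replies stand.

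Three others stand in part. The SAP says the test gives evidence, not proof, and leaves fuller causal analysis to a separate paper; but Table 2 still uses the word causal, and Protocol 10.2 explicitly sets the result against a non-specific effect. Supplementary Table 6 cross-tabulates clinician belief before and after by test result, which would help to expose an effect unrelated to the result; but it is descriptive and concerns belief, not prescribing. The false signals in step 3 (ratios of 0.67 to 0.75 in the strong settings) are much weaker than the planned 0.25 or 0.083, and Table 2 shows the stratum odds ratios, so a reader could judge size. Prescribing that rose in virus-negative patients while falling in virus-positive ones would also be hard to explain without the result.

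None of this supplies the missing step from balance between arms to the cause of the difference between strata.

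**Conclusion.** The point holds as one of inference and wording, with a cheap check missing. The interaction validly tests whether the POCT effect differs by virus status. Reading it as the causal role of the result needs the added assumption that no other modifier of the POCT effect is linked to virus status.

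Under assumed strong links and a large effect unrelated to the result, the planned test rejects in roughly 10-20% of trials in which the result is ignored, and more only at extreme settings. Under mild links or milder effects it stays near 5-7%. The documents contain no data on virus status by belief, age or lung disease, so the true figure cannot be placed within that range.

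A reader might infer that a significant interaction would probably be spurious, or that the bias must favour the hypothesis. The documents support neither. One of the settings above gives a ratio slightly over 1, and a non-specific effect with a constant relative risk of 0.75 gives a ratio of 0.60/0.43 = 1.4 (14% rejection), which points away from the hypothesis. Nor is the planned test shown to lack power for want of these terms: the gain in step 6 depends on belief being strongly prognostic. The primary outcome and its analysis are untouched.

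**What to change.** Keep the planned Group × Virus interaction as the main mechanistic test, and make two changes.

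1. In SAP 4.8, replace the causal sentence with: the interaction supports a role of the result on the assumption that no other modifier of the POCT effect is linked to virus status. Align Protocol 10.2 and the Table 2 row label with it.
2. Add to Table 2 a sensitivity model that includes pre-randomisation clinician belief (Study Clinician Views item 1, Step 2), age group and chronic lung disease, each with its interaction with allocated group. Pre-specify how the five-level belief item is coded, and show the Group × Virus estimate beside the planned one. Main effects alone are not enough (step 4).

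No new data are needed: belief is an eligibility item, and the other two stratify the randomisation. The cost is a few more parameters and, if the modifiers are not prognostic, some power in the sensitivity model (step 6). For that reason it should not replace the main test. It also addresses only measured modifiers, so the stated assumption is still needed.

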## 5. PRIMARY RESULTS PAPER FIGURES AND TABLES

Figure 1. CONSORT flowchart

[figure not shown]

**Table 1.** Baseline participant characteristics

|                                                                                               | Intervention (n=XX) |                      | Control (n=XX) |                      |
|-----------------------------------------------------------------------------------------------|---------------------|----------------------|----------------|----------------------|
|                                                                                               | N*                  | Mean (SD) /
n (%) | N*             | Mean (SD) /
n (%) |
| Demographics                                                                           |                     |                      |                |                      |
| Number of males (%)                                                                           | XX                  | XX (XX%)             | XX             | XX (XX%)             |
| Mean age in years (SD)                                                                        | XX                  | XX (XX)              | XX             | XX (XX)              |
| Number age ≥16 years (%)                                                                      | XX                  | XX (XX%)             | XX             | XX (XX%)             |
| Number white ethnic group (%)                                                                 | XX                  | XX (XX%)             | XX             | XX (XX%)             |
| Medical history                                                                        |                     |                      |                |                      |
| Chronic lung disease present                                                                  | XX                  | XX (XX%)             | XX             | XX (XX%)             |
| Has consulted for RTI in past 12 months                                                       | XX                  | XX (XX%)             | XX             | XX (XX%)             |
| Antibiotic treatment received in the past 12 months                                           | XX                  | XX (XX%)             | XX             | XX (XX%)             |
| Any positive COVID tests in the past 3 months?                                                | XX                  | XX (XX%)             | XX             | XX (XX%)             |
| Any previous antibiotic/ antiviral treatment for the patient's current illness?               | XX                  | XX (XX%)             | XX             | XX (XX%)             |
| Clinical measures                                                                      |                     |                      |                |                      |
| Number with oxygen saturation < 94% (%)                                                       | XX                  | XX (XX%)             | XX             | XX (XX%)             |
| Number with temperature > 38°C (%)                                                            | XX                  | XX (XX%)             | XX             | XX (XX%)             |
| Number with abnormal pulse in beats per minute (%)                                            | XX                  | XX (XX%)             | XX             | XX (XX%)             |
| Number with abnormal respiratory rate in breaths per minute (%)                               | XX                  | XX (XX%)             | XX             | XX (XX%)             |
| Signs present, where assessed                                                          |                     |                      |                |                      |
| Pallor                                                                                        | XX                  | XX (XX%)             | XX             | XX (XX%)             |
| Inter/subcostal recession                                                                     | XX                  | XX (XX%)             | XX             | XX (XX%)             |
| Cervical glands                                                                               | XX                  | XX (XX%)             | XX             | XX (XX%)             |
| Inflamed pharynx or tonsils                                                                   | XX                  | XX (XX%)             | XX             | XX (XX%)             |
| Pus on tonsils                                                                                | XX                  | XX (XX%)             | XX             | XX (XX%)             |
| Wheeze                                                                                        | XX                  | XX (XX%)             | XX             | XX (XX%)             |
| Crackles or crepitations                                                                      | XX                  | XX (XX%)             | XX             | XX (XX%)             |
| Bronchial breathing                                                                           | XX                  | XX (XX%)             | XX             | XX (XX%)             |
| Erythema of ear drum with dullness, cloudiness or bulging, consistent with acute otitis media | XX                  | XX (XX%)             | XX             | XX (XX%)             |

aNumber of participants providing data for this measure

Table 1 continued.

|                                                                                                           | Intervention (n=XX) |                   | Control (n=XX) |                   |
|-----------------------------------------------------------------------------------------------------------|---------------------|-------------------|----------------|-------------------|
|                                                                                                           | N a      | Mean (SD) / n (%) | N a | Mean (SD) / n (%) |
| Clinician’s diagnosis                                                                                     |                     |                   |                |                   |
| Acute otitis media                                                                                        | XX                  | XX (XX%)          | XX             | XX (XX%)          |
| Common cold                                                                                               |                     | XX (XX%)          |                | XX (XX%)          |
| Acute sinusitis                                                                                           |                     | XX (XX%)          |                | XX (XX%)          |
| Acute pharyngitis or tonsillitis                                                                          |                     | XX (XX%)          |                | XX (XX%)          |
| Sore throat                                                                                               |                     | XX (XX%)          |                | XX (XX%)          |
| Acute laryngitis                                                                                          |                     | XX (XX%)          |                | XX (XX%)          |
| Acute cough                                                                                               |                     | XX (XX%)          |                | XX (XX%)          |
| Acute bronchitis                                                                                          |                     | XX (XX%)          |                | XX (XX%)          |
| Chest infection                                                                                           |                     | XX (XX%)          |                | XX (XX%)          |
| Acute lower respiratory tract infection                                                                   |                     | XX (XX%)          |                | XX (XX%)          |
| Infective exacerbation of chronic lung disease                                                            |                     | XX (XX%)          |                | XX (XX%)          |
| Influenza                                                                                                 |                     | XX (XX%)          |                | XX (XX%)          |
| Covid-19                                                                                                  |                     | XX (XX%)          |                | XX (XX%)          |
| Other                                                                                                     |                     | XX (XX%)          |                | XX (XX%)          |
| Clinician’s overall assessment                                                                            |                     |                   |                |                   |
| My gut feeling is ‘Something is wrong’                                                                    | XX                  | XX (XX%)          | XX             | XX (XX%)          |
| How unwell do you consider the participant to be:
mean (SD) rating on scale 0: well to 10: very unwell | XX                  | XX.X (XX.X)       | XX             | XX.X (XX.X)       |

aNumber of participants providing data for this measure

**Table 2.** Antibiotic prescribing at appointment 2 on day of presentation (primary outcome).

|                                                                                | Intervention
n/N(%) | Control
N(%) | Odds Ratioa
(95% Conf. Interval) | P value     |
|--------------------------------------------------------------------------------|--------------------------------|-------------------------|--------------------------------------------------------|--------------------|
| Primary analysis                                                        |                                |                         |                                                        |                    |
| All antibiotic prescriptions                                                   | XX/XXX (XX%)                   | XX/XXX (XX%)            | XX.XX (XX.XX, XX.XX)                                   | 0.XXX              |
| Immediate antibiotic prescriptions                                             | XX/XXX (XX%)                   | XX/XXX (XX%)            |                                                        |                    |
| Delayed antibiotic prescriptions                                               | XX/XXX (XX%)                   | XX/XXX (XX%)            |                                                        |                    |
|                                                                                |                                |                         |                                                        |                    |
| Sensitivity analyses                                                    |                                |                         |                                                        |                    |
| Adjusting for practice identifier                                              |                                |                         | XX.XX (XX.XX, XX.XX)                                   | 0.XXX              |
| Adjusting for baseline imbalance                                               |                                |                         | XX.XX (XX.XX, XX.XX)                                   | 0.XXX              |
|                                                                                |                                |                         |                                                        |                    |
| Per protocol population                                                        | XX/XXX (XX%)                   | XX/XXX (XX%)            | XX.XX (XX.XX, XX.XX)                                   | 0.XXX              |
|                                                                                |                                |                         |                                                        |                    |
| Pre-specified subgroup analyses                                         |                                |                         |                                                        |                    |
| Age at baseline                                                                |                                |                         |                                                        | 0.XXX b |
| Child (age <16 years)                                                          | XX/XXX (XX%)                   | XX/XXX (XX%)            | XX.XX (XX.XX, XX.XX)                                   |                    |
| Adult (age 16+ years)                                                          | XX/XXX (XX%)                   | XX/XXX (XX%)            | XX.XX (XX.XX, XX.XX)                                   |                    |
|                                                                                |                                |                         |                                                        |                    |
| Chronic lung disease at baseline                                               |                                |                         |                                                        | 0.XXX b |
| Yes                                                                            | XX/XXX (XX%)                   | XX/XXX (XX%)            | XX.XX (XX.XX, XX.XX)                                   |                    |
| No                                                                             | XX/XXX (XX%)                   | XX/XXX (XX%)            | XX.XX (XX.XX, XX.XX)                                   |                    |
|                                                                                |                                |                         |                                                        |                    |
| Participant – Doctor disagreement at baseline c                     |                                |                         |                                                        | 0.XXX b |
| Yes                                                                            | XX/XXX (XX%)                   | XX/XXX (XX%)            | XX.XX (XX.XX, XX.XX)                                   |                    |
| No                                                                             | XX/XXX (XX%)                   | XX/XXX (XX%)            | XX.XX (XX.XX, XX.XX)                                   |                    |
|                                                                                |                                |                         |                                                        |                    |
| Causal mechanistic analysis – per protocol population                   |                                |                         |                                                        |                    |
| Virus detected on POCT RM (comparison group result from laboratory) |                                |                         |                                                        | 0.XXX b |
| Yes                                                                            | XX (XX%)                       | XX (XX%)                | XX.XX (XX.XX, XX.XX)                                   |                    |
| No                                                                             | XX (XX%)                       | XX (XX%)                | XX.XX (XX.XX, XX.XX)                                   |                    |

a. Odds ratio and confidence interval, from a logistic regression model, adjusting for participant age and chronic lung disease status

b. p-value for interaction term, testing the null hypothesis of equal odds ratios in the population between the two subgroups

c. Participant believes antibiotics are needed to treat the RTI, doctor does not believe or is unsure that antibiotics are needed

**Table 3** Symptom measures

